#### Collection of study data

Baseline data were gathered by the researchers masked to allocation status of the units via direct observation of each individual ward and its facilities, an interview with the ward manager (to collate routine data on incidents and wards costs), and surveys of staff and service users. The unit’s link person produced a timetable for the data collection visit that specified what time and where each component of the visit would take place (e.g., managers’ interview, tour of the wards, meetings with patients and staff). All service users were asked to take part in the survey except those where clinical staff judged that their current mental state meant they should not be approached by a member of the research team. Participants were given the option of completing and returning the questionnaires on the day of the assessment or sending them back to the research team in a pre-paid envelope. Pre-paid envelopes and blank questionnaires to complete were left for those staff members that were not scheduled on shift during the visit and for service users on community leave. No identifiable information about staff and service users were recorded. Twelve months after the collection of baseline data, a member of the research team who was again masked to allocation status of the unit arranged to visit each site again for a follow-up assessment. The instruments used at baseline were administrated for a second time at follow-up in the same manner.

#### Sample size

The sample size for the study was based on the primary hypothesis: the quality of the physical environment and facilities in wards that participate in the network would be higher 12 months after randomization than in those wards that do not participate in the network. A previous investigation with medium secure wards that took part in the quality network showed an increase in the proportion of standards met equivalent to a 10 % increase during the first year of membership of the network [19].

Assuming no change in outcome in the control arm, the sample size was based on detecting a 10 % difference between groups, equivalent to 10 units of the environmental checklist score. The sample size was calculated assuming an ANCOVA analysis, with the baseline scores used as the covariate. Based on preliminary data, a correlation of 0.53 between baseline and outcome scores was assumed. A standard deviation of 13.3 for the primary outcome was assumed (estimated using baseline data from the first 32 wards that took part in the trial). Using a 5 % significance level and 90 % power, it was calculated that 54 wards were required (27 in the active arm and 27 in the control arm of the trial). To take account of 10 % drop out from the study, we increased the sample size to 60 wards.

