**Methods:**

Standalone low secure units in England and Wales that expressed an interest in joining the quality improvement network were recruited for the study from 2012 to 2014. Thirty-eight units were randomly allocated to either the active intervention (participation in the network *n* = 18) or a control arm (delayed participation in the network *n* = 20). Using a 5 % significance level and 90 % power, it was calculated that a sample size of 60 wards was required taking into account a 10 % drop out. A total of 75 wards were assessed at baseline and 8 wards dropped out the study before the data collection at follow up. Researchers masked to the allocation status of the units assessed all study outcomes at baseline and follow-up 12 months later. The primary outcome is the quality of the physical environment and facilities on the wards. The secondary outcomes are: safety of the ward, patient-rated satisfaction with care and mental well-being, staff burnout, training and supervision. Relative to control wards, it is hypothesized that the quality of the physical environment and facilities will be higher on wards in the active arm of the trial 12 months after randomization.

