#### Randomization and blinding

Some wards were part of a unit that included other wards on the same site. While there may be differences in services provided by different wards on the same unit, management is often shared and we judged that there was considerable potential for contamination of the effects of the intervention across wards on the same unit. We therefore randomized units rather than wards. The Quality Network team emailed the contact details of eligible services to an independent team based at Imperial College London which was in charge of the randomization process. This team used a web-based randomization programme and a randomization ratio of 1:1, early versus delayed participation in the network. Randomization was stratified according to the size of the unit (whether they contained up to four, or more than four wards). Following randomization of the 38 eligible units, 18 (47 %) were allocated by the independent team to the active arm and 20 (53 %) to the control arm of the study. The list of early and late participation units was then sent back to the Quality Network team that informed the units of their membership status.

Once all the units were informed of their allocation status, the quality network team sent the research team the full list of units enrolled for the study without any reference to their group membership. The research group then made contact with the units and arranged for baseline data collection. The units’ link person and all staff members were repeatedly reminded that the researcher collecting study data must not be told which arm of the trial they were in. In the event of accidental unmasking of a researcher, all further data were collected by a second researcher who was masked to the allocation status of the unit.

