## Discussion

This study provides an opportunity to explore the impact of participation in a peer network on the quality of inpatient mental health services. By comparing the quality of the physical environment and facilities of units that do and do not take part in a network we will able to find out what, if any, benefit membership of a peer network delivers. In addition, the study will explore whether participation in a quality network has any impact on staff and patient outcomes. To our knowledge this is the first time that a randomized evaluation of participation in a peer-led network has been conducted that will examine patient and staff safety, patient experience and the clinical effectiveness of care that patients receive.

Quality networks are one of a broad range of initiatives that services may use to try to improve the quality of care they provide. All such initiatives have costs as well as potential benefits, both in terms of direct costs of delivering the programme and time spent by staff completing self and peer reviews. Strengths of this study are that it is adequately powered to examine clinically important differences in service quality and the wide geographical area that the units were recruited from. By integrating the trial into the development of a new quality improvement network we ensured that nearly all eligible services took part in the study.

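### The 54 wards (60 with dropout) stated for 90% power assume independent wards, although units of about two wards each were randomised

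*Protocol article*

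**What the plan says.** The Sample size section gives a complete calculation. The error rate and power are set by "Using a 5 % significance level and 90 % power". The target is fixed where "the sample size was based on detecting a 10 % difference between groups, equivalent to 10 units of the environmental checklist score". For the spread, "A standard deviation of 13.3 for the primary outcome was assumed", and for the ANCOVA, "a correlation of 0.53 between baseline and outcome scores was assumed". From these, "it was calculated that 54 wards were required (27 in the active arm and 27 in the control arm of the trial"), and 10% dropout takes the total to 60. The abstract repeats the result: "it was calculated that a sample size of 60 wards was required taking into account a 10 % drop out".

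The Randomization and blinding section says "We therefore randomized units rather than wards", because wards in one unit often share management and contamination between them was expected. There were 38 units (18 active, 20 control) holding 75 wards. The abstract calls the trial cluster randomised.

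The Data management and analysis section compares 12-month checklist scores by ANCOVA with the ward's baseline score as covariate. It models clustering only for staff and patients within wards.

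The Discussion states: "Strengths of this study are that it is adequately powered to examine clinically important differences in service quality".

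**The concern.** No ICC, design effect or number of units enters the calculation. If wards in a unit resemble each other, 54 of them carry less information than 54 independent wards, and the stated requirement is too small for the stated power.

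The article itself gives reasons to expect some resemblance. Shared management is the reason given for randomising units, and at least one checklist item (the external perimeter) describes the service and not the ward.

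At stake is how the primary result will be read. A null result would be set against a 90% power figure, and a claim of adequate power, that the calculation does not establish for this design.

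**Working it through.** **Inputs from the article.** Difference 10 points, SD 13.3, baseline–outcome correlation 0.53, alpha 5% (sidedness not stated), power 90%, dropout 10%, 38 units, 75 wards at baseline, and 8 wards lost, leaving 67.

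**Assumptions.** The article gives neither the ICC nor the unit-size distribution. The ICC below is the residual one, after baseline adjustment, because the design effect multiplies the residual variance. Unit sizes are taken as equal, or with a coefficient of variation (CV) of 0.6 or 0.8.

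**Step 1: reproduce the stated figure.**
- Residual SD = 13.3 × √(1 − 0.53²) = 13.3 × √0.7191 = 11.28.
- Wards per arm = 2 × (1.960 + 1.2816)² × 11.28² / 10² = 26.7, so 27 per arm and 54 in total.
- 54 / 0.9 = 60.

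One-sided 5% would give 22 per arm, and no baseline adjustment 38, so the two-sided ANCOVA formula is the one used. Power at 27 per arm is 90.3%. The match is exact with a design effect of 1, which leaves no hidden allowance for clustering.

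**Step 2: the same formula with a design effect.** DE = 1 + ((CV² + 1) × m − 1) × ICC, with m = 75/38 = 1.97. Required wards = 53.46 × DE. Power at 54 wards = Φ(10 / (11.28 × √(2 × DE / 27)) − 1.96).

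Example at ICC 0.3 with equal sizes: DE = 1 + 0.974 × 0.3 = 1.29. The standard error is 11.28 × √(2 × 1.29 / 27) = 3.49, and Φ(2.87 − 1.96) = 0.82.

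| Residual ICC | DE, equal sizes | Power at 54 wards | Analysed wards for 90% (with dropout) | Power at 54, CV 0.6 | Analysed wards for 90%, CV 0.6 |
|---|---|---|---|---|---|
| 0 | 1.00 | 90.3% | 54 (60) | 90.3% | 54 |
| 0.1 | 1.10 | 87.5% | 59 (66) | 85.4% | 63 |
| 0.3 | 1.29 | 81.8% | 70 (78) | 75.7% | 81 |
| 0.5 | 1.49 | 76.2% | 80 (89) | 67.0% | 99 |

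If 54 wards were instead spread over all 38 units (1.42 per unit, equal sizes), power would be 89.1%, 86.6% and 84.2% at ICC 0.1, 0.3 and 0.5. That is a smaller loss, but still below 90%.

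**Step 3: the trial as recruited.** 75 − 8 = 67 followed wards, or 67/38 = 1.76 per unit if every unit remained. Arms are taken as equal in size.

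| Residual ICC | Equal sizes | CV 0.6 | CV 0.8 |
|---|---|---|---|
| 0 | 95.2% | 95.2% | 95.2% |
| 0.1 | 93.8% | 92.5% | 91.4% |
| 0.3 | just above 90% | 86.1% | 82.6% |
| 0.5 | 87.0% | 79.5% | 73.9% |

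Power stays at 90% while DE ≤ 67/53.46 = 1.25. With 1.76 wards per unit this means an ICC up to 0.33 (equal), 0.18 (CV 0.6) or 0.13 (CV 0.8). With 1.97 per unit the limits are 0.26, 0.15 and 0.11.

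These are normal-approximation figures, as in the plan. A noncentral t on 38 − 3 = 35 degrees of freedom lowers the equal-size values to 88.9% at ICC 0.3 and 85.1% at 0.5.

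**Step 4: the ANCOVA as described.** A ward-level test that ignores units does not lose power in this way. It understates the standard error by √DE, so its true two-sided error rate is 2 × Φ(−1.96/√DE): about 6.2% at DE 1.1 and 8.6% at DE 1.3.

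**The case against.** The strongest defence is that the arithmetic is right, that the ICC needed to show a loss is nowhere in the article, and that 54 analysed wards never occurred. The trial recruited 75 and followed 67, which covers a modest design effect. Much of what wards on one site share, such as the perimeter or airlock, persists over time and may be absorbed by the baseline covariate, leaving a small residual ICC. The claim of adequate power names no percentage.

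Most of this stands, and it limits the point. A reader might infer that the trial lacks the power claimed for it. The article does not support that: the answer depends on an ICC and a unit-size distribution that it does not give. The existence of a stratum of units with more than four wards, against a mean of about two, suggests unequal sizes but does not fix the CV.

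Method also matters. A noncentral t on 24 degrees of freedom gives 87.8% for 54 wards even at ICC 0. Comparing such figures with the plan's 90% would blame clustering for about 2.5 points that come from the change of method.

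The defence does not rescue the stated requirement. It reproduces to the integer with no design effect, so an ICC given in a fuller document could not already be inside it. Nor does the planned ANCOVA help, because ignoring units exchanges the power loss for an inflated error rate.

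**Conclusion.** The point holds for the stated requirement. 54 wards, and 60 with dropout, is the size for independent wards and not for the unit-randomised design. Assuming 1.97 wards per unit and equal sizes, power at 54 wards is about 87.5%, 82% and 76% at a residual ICC of 0.1, 0.3 and 0.5, and lower if unit sizes vary. Below an ICC of about 0.05 the loss is under 2 points (88.9% at 0.05), but the shared management that the article describes makes a value near zero hard to take for granted.

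It is not shown that the completed trial is underpowered. With 67 wards and equal sizes, power is about 90% or better up to an ICC of roughly 0.3. With assumed CVs of 0.6 to 0.8 it falls below 90% from an ICC of about 0.11 to 0.18. All these powers presuppose an analysis that accounts for units.

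**What to change.** No further recruitment is called for.

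- In the Sample size section and the abstract, say that 54/60 assumes independent wards.
- Report the design effect from the actual unit sizes, and the power or detectable difference for 38 units and 67 followed wards, over a range of residual ICCs and by one stated method. The ICC must be the baseline-adjusted one. A raw ICC from the 32 baseline wards used for the SD is a different quantity.
- Tie that power to a primary analysis that accounts for unit: a unit random effect with a small-sample correction, or a unit-level ANCOVA.
- Qualify the claim of adequate power in the Discussion to match.

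The cost is a text change and a little analysis work. The stated power becomes less favourable.

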#### Data management and analysis

All data were entered electronically into a database. Once data collection was completed, 100 % of the scores of the primary outcome measure were double checked against source data for accuracy. All analysis will follow the intention-to-treat principle. Descriptive analyses including tables and graphs of baseline organisational processes and clinical outcomes will be produced for each of the two arms of the trial.

The scores of the primary outcome measure (QELS checklist scores at 12 months) will be compared between the two groups using analysis of covariance (ANCOVA). The scores at 12 month will be considered as the outcome measure, with the wards’ scores at baseline used as a covariate.

The scores of the secondary outcome variables measured at the ward level and on continuous scales (e.g., number of untoward incidents), will be analysed using the unpaired *t*-test or Mann–Whitney test depending on the data distribution. Most secondary outcome variables are measured at the staff or patient level (e.g., staff burnout, service users mental wellbeing and satisfaction with care). It is anticipated that there will be clustering of outcomes as a result of participants receiving interventions on different wards. Such clustering violates the assumption that observed outcomes of participants are independent and can result in increased standard errors [20, 21]. To take account of this, these outcomes will be analysed using a two level multilevel regression models with patients/staff at level one and the wards as the second level. When measured, baseline values of each outcome will be used as a covariate in the analysis. Additional exploratory analysis will investigate possible predictors of the primary outcome (environmental checklist scores at 12 months). This analysis will be performed using multiple linear regression.

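### The tests named for continuous ward-level secondary outcomes cannot use the ward baseline values that the trial collected and that the plan says will be a covariate when measured

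*Protocol article*

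**What the plan says.** All references are to the protocol article.

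- **Data management and analysis**, general statement: "All analysis will follow the intention-to-treat principle".
- **Same section, primary outcome**: ANCOVA of the QELS score. "The scores at 12 month will be considered as the outcome measure", "with the wards’ scores at baseline used as a covariate".
- **Same section, ward-level secondary outcomes**: outcomes on continuous scales are compared by an unpaired t-test or a Mann-Whitney test, chosen by their distribution. The example given is the number of untoward incidents.
- **Same section, staff and patient outcomes**: two-level models with wards at the second level. The next sentence says that baseline values of each outcome, where measured, will be covariates.
- **Secondary outcome measures**: ward safety includes counts of absconsions and untoward incidents over the previous 6 months.
- **Collection of study data**: the baseline visit included a ward-manager interview that collected routine incident data, and the baseline instruments were used again at follow-up.
- **Abstract, Methods**: "A total of 75 wards were assessed at baseline and 8 wards dropped out the study before the data collection at follow up".

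**The concern.** The two statements about secondary outcomes do not fit together. If the baseline-covariate sentence covers every secondary outcome, it contradicts the tests named for the ward-level ones, because a t-test or Mann-Whitney test conditions on nothing but arm. If it covers only the multilevel models, the ward-level outcomes are the only ones left unadjusted, and no reason is given.

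The second reading is also an odd choice in its own terms. Wards can be linked from baseline to 12 months. Individual staff and patients cannot: no identifiable information was recorded, and the Discussion says that individual-level change cannot be examined. The outcomes whose baseline is easiest to use would be the ones that do not use it.

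Two things are at stake for the ward-level safety comparisons. One is precision. The other is protection against bias when wards are lost: a comparison that ignores baseline is distorted if wards with unusual baseline values drop out more often in one arm, whereas a comparison that conditions on baseline is not.

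**Working it through.** **1. The plan's own figure, and what it says about baseline adjustment.** Inputs from the Sample size section: difference 10 points, SD 13.3, baseline-outcome correlation 0.53, 5% significance (two-sided reproduces the figure), 90% power, 10% drop-out.

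- Residual SD = 13.3 × √(1 − 0.53²) = 11.28.
- Wards per arm = 2 × [(1.960 + 1.282) × 11.28 / 10]² = 26.73, rounded up to 27, so 54 in total. Then 54 / 0.90 = 60. Both stated figures reproduce.
- The same calculation without baseline adjustment needs 38 per arm. The plan therefore relies on the baseline covariate for its primary outcome.

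**2. Wards with follow-up.** 75 − 8 = 67; 8/75 = 10.7% lost.

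**3. Precision.** With correlation r, adjustment multiplies the residual variance by 1 − r². The article gives r only for QELS, so its use for the safety outcomes is an assumption.

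- At r = 0.53: 1 − 0.281 = 0.719, so the standard error falls to √0.719 = 0.85 of its unadjusted value.
- At r = 0 there is no gain.
- For scale, for a difference of 10/13.3 = 0.75 SD with 67 wards treated as independent, power is 86.8% unadjusted and 95.2% adjusted at r = 0.53.

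**4. Bias when loss depends on baseline.** Simulation with no true effect, 37 and 38 wards per arm (assumed), r = 0.53, normal outcomes and 8 wards lost. Entries are the mean estimated difference, in SD of the outcome.

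| Split of the 8 losses | Lowest-baseline wards lost: unadjusted | Same: baseline-adjusted | Lowest-outcome wards lost: unadjusted | Same: baseline-adjusted |
|---|---|---|---|---|
| 8:0 | 0.19 | about 0 | 0.37 | 0.28 |
| 6:2 | 0.10 | about 0 | 0.18 | 0.14 |
| 4:4 | about 0 | about 0 | 0.01 | 0.01 |

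A check by hand: removing the lowest 8 wards of one arm on a variable shifts that arm's mean on it by about 0.37 SD (the 8:0 lowest-outcome column). If the variable is baseline, the outcome shifts by r times that, 0.53 × 0.37 = 0.20, in line with the simulated 0.19. The bias therefore scales with r and vanishes at r = 0.

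**5. Size against sampling error.** At 8:0 from one arm, 29 and 38 wards remain, so the unadjusted standard error is about √(1/29 + 1/38) = 0.247 SD and the bias is 0.192/0.247 = 0.78 standard errors. At 6:2, 31 and 36 remain: √(1/31 + 1/36) = 0.245 and 0.098/0.245 = 0.40 standard errors.

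**The case against.** **The bias figures rest on assumed splits.** This stands. Losses by arm are not in the text shown, and the flow diagram is not reproduced. The 8:0 case needs every loss to fall in one arm and among its lowest-baseline wards. No differential retention is reported, retention efforts are described for all services, and waiting to join the network may itself have been a reason for control units to stay. An even split with the same mechanism gives almost nothing. The figures are a range, not an estimate.

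**The baseline-covariate sentence may already cover ward-level outcomes.** It may. The named tests still could not carry it out, so the text needs reconciling either way.

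**A reader might infer more.** It is tempting to say that the intention-to-treat claim is false because only 67 wards can be analysed, and that the plan lacks imputation and a tipping-point analysis. The document does not support this. It states intention-to-treat as a principle, and analysis by allocated arm satisfies it. Nothing moves wards between arms or excludes units for poor participation. Nothing says that wards without 12-month data are dropped, and imputation could precede any of the named tests. Missing-data handling and sensitivity analyses are commonly left to the SAP or full protocol, which are not shown. The primary ANCOVA already conditions on baseline, so even an analysis of wards with 12-month data is valid if loss depends only on arm and baseline. Nor does the loss undermine stated power: 67 exceeds the 54 required, and 10.7% is close to the planned 10%.

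**Conclusion.** The point holds for continuous ward-level secondary outcomes only. The tests named for them cannot use baseline values that were collected, and they disagree with, or are left out of, the sentence on baseline covariates.

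The certain consequence is that available information is discarded. The precision cost depends on a correlation that the article does not give for these outcomes: nil at r = 0, about 15% of the standard error at r = 0.53. Bias is possible but not shown: about 0.19 SD at 8:0, 0.10 SD at 6:2 and nil at 4:4, if the lowest-baseline wards are lost.

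These figures assume r = 0.53, near-equal arms, normal outcomes and wards independent within units. Incident counts are likely to be skewed, so SD units are only indicative, and the simulation compared means, not ranks. Positive correlation between wards of one unit would raise the standard error and make the bias smaller relative to it.

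Baseline adjustment does not cure loss that depends on the unseen 12-month value; it only reduces that bias (0.37 to 0.28 SD at 8:0). It also treats baseline as unaffected by allocation, although baseline visits were arranged after units had been told their arm. The primary ANCOVA already makes that assumption. This is a modest point about secondary outcomes and does not touch the primary result.

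**What to change.** In Data management and analysis, replace the unpaired t-test and Mann-Whitney test for ward-level secondary outcomes with a regression of the 12-month value on arm and the ward's baseline value. Use a count model for incident and absconsion counts and a linear model where the scale and distribution allow it. State that the baseline-covariate sentence applies to these outcomes, so that method and sentence agree.

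No new data are needed, since the ward-level items were collected at both visits. The cost is a little more modelling work and a model assumption in place of a rank test. Where that assumption is in doubt, the Mann-Whitney test can be kept as a supporting check. The primary analysis and the intention-to-treat statement need no change on this account.

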### Study procedures

#### Recruitment and consent procedures

The recruitment of the low secure units was carried out by the Quality Network for Forensic Mental Health Services team who publicised the study on the network’s website. Recruitment took place over three years as part of an annual cycle of recruitment, self-review and peer review between June 2012 and June 2014. At the beginning of each peer-review cycle, the eligible units that agreed to take part in the network were randomized to the active or control arm of the trial (see study setting and sample section for details on eligibility). Thirty-eight units in total took part in the study (75 wards). Each unit nominated a link person to communicate with the research team to arrange the data collection visit. The link person was in charge of circulating the study information sheet to staff and patients at least two weeks prior the data collection visit by the researcher and coordinate the logistic of the visit between the researcher, staff and patients on the wards. The researcher was escorted by staff members on the day of the visit to observe the wards’ facilities and complete the environmental checklist. During the escorted visit the researcher engaged with staff and patients by providing further details about the study and sought informed consent to complete the study survey from those who were willing to participate. The patients who agreed to participate were assisted by the researcher or staff to fill in their survey if needed. In order to maximize completeness of data collection, the research team made every effort to monitor participants’ retention from baseline to follow-up. Retention strategies included consistent and frequent contact of the research team with service in preparation for the data collection visits.

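### The primary ANCOVA treats wards as independent although units were randomised, so its standard error is too small if wards in a unit remain correlated after baseline adjustment

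*Protocol article*

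**What the plan says.** The abstract of the protocol article calls the trial cluster randomised. Under Randomization and blinding it states "We therefore randomized units rather than wards", because "management is often shared and we judged that there was considerable potential for contamination of the effects of the intervention across wards" on one site. The same section reports that "18 (47 %) were allocated by the independent team to the active arm and 20 (53 %) to the control arm of the study". It adds: "Randomization was stratified according to the size of the unit (whether they contained up to four, or more than four wards"). Recruitment and consent procedures gives the totals: "Thirty-eight units in total took part in the study (75 wards"). The abstract reports that 8 wards dropped out before follow-up, which leaves 75 − 8 = 67.

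Under Data management and analysis, the QELS scores at 12 months "will be compared between the two groups using analysis of covariance (ANCOVA"), with the ward's own baseline score as covariate. No unit random effect, cluster-robust error or unit-level summary is stated for this comparison. The section does discuss clustering, but only for outcomes measured on patients and staff, and the top level of those models is the ward. The randomised unit appears in no stated model.

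The Sample size section counts wards (27 per arm, 54 in all, 60 after dropout) and mentions neither an ICC nor a design effect.

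**The concern.** Allocation was by unit, so the independent pieces of information about the arm effect are the 38 units. An ordinary ANCOVA on wards computes its standard error as if each ward had been allocated separately. That is correct only if, once baseline is adjusted for, wards in one unit are no more alike than wards in different units.

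The article gives reasons to doubt this:

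- Management is often shared within a unit.
- Several items of the QELS checklist (external perimeter, visitor facilities, airlock, multi-faith room) may well be common to wards on one site.
- The peer review, feedback and local report are delivered to the service, so changes during the year can reach its wards together.

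At stake are the p-value and confidence interval of the primary comparison.

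**Working it through.** **Inputs from the article.** Difference 10 points, SD 13.3, baseline–outcome correlation 0.53, 5% significance, 90% power, 10% dropout (Sample size); 38 units and 75 wards (Recruitment and consent procedures); 67 wards at follow-up (from the abstract). **Not in the article:** the ICC and the distribution of unit sizes. Both are assumed below.

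**1. Reproduce the stated sample size.** The SD after baseline adjustment is 13.3 × √(1 − 0.53²) = 11.28. Wards per arm = 2 × [11.28 × (1.960 + 1.282)/10]² = 26.7, rounded up to 27. That gives 54 wards, and 54/0.90 = 60. Sidedness is not stated; a two-sided test fits, whereas one-sided gives 22 per arm. The match is exact with a design effect of 1, so the calculation treats wards as independent, as the analysis does.

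**2. Design effect.** DE = 1 + (m* − 1) × ICC, where m* = Σm²/Σm and ICC is the correlation of residuals within a unit after baseline adjustment.

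- Equal sizes, wards followed up, all 38 units assumed still present: m* = 67/38 = 1.76.
- Equal sizes, wards at baseline: m* = 75/38 = 1.97.
- Illustrative unequal sizes (20 units of 1 ward, 9 of 2, 4 of 3, 2 of 4, 2 of 5, 1 of 7; 38 units, 75 wards): m* = 223/75 = 2.97.

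**3. True two-sided alpha of the nominal 5% test:** 2 × [1 − Φ(1.96/√DE)].

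| Residual ICC | Equal, m* 1.76: DE, alpha | Equal, m* 1.97: DE, alpha | Unequal, m* 2.97: DE, alpha |
|---|---|---|---|
| 0 | 1.00, 5.0% | 1.00, 5.0% | 1.00, 5.0% |
| 0.1 | 1.08, 5.9% | 1.10, 6.1% | 1.20, 7.3% |
| 0.3 | 1.23, 7.7% | 1.29, 8.5% | 1.59, 12.0% |
| 0.5 | 1.38, 9.5% | 1.49, 10.8% | 1.99, 16.4% |

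The ratio of true to reported standard error is √DE. From the first to the last column it is 1.04–1.09 at ICC 0.1, 1.11–1.26 at 0.3 and 1.18–1.41 at 0.5.

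**4. Check by simulation under the null** (38 units, 18 v 20, 75 wards, correlation 0.53, 8,000 runs per setting). At ICC 0/0.1/0.3/0.5 the ward-level ANCOVA rejected in 5.2/5.5/8.8/11.1% of runs with near-equal sizes. With an unequal set (20 units of 1, 8 of 2, 5 of 3, 1 of 4, 4 of 5) it rejected in 5.3/7.2/11.3/15.5%. An ANCOVA on unit means stayed between 4.6% and 5.3% in both.

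**5. How far baseline adjustment helps.** Suppose the whole correlation of 0.53 came from a stable unit effect. The residual unit variance is then 0.47² × 0.53 = 0.117, out of a total residual variance of 1 − 0.53² = 0.719, so the residual ICC is 0.16. True alpha is about 6.9% (equal sizes, m* = 1.97) or 8.8% (the unequal sizes of step 2).

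**The case against.** The strongest reply concerns size. What matters is correlation after baseline adjustment, and features such as a perimeter or an airlock are largely stable, so much of their shared variance is already in the baseline score. Step 5 shows that stable site features alone need not take the residual ICC above about 0.16. A residual ICC of 0.3 or more needs changes during the year that affect a unit's wards together. That is plausible for an intervention delivered per service and for shared management, but the article gives no figure. The stated worry about contamination concerns spread of the intervention's effects and is only indirect evidence of residual correlation under the null. The unequal-size figures rest on an assumed distribution: the article gives a stratification cut-point, not how many units lay above it. All of this stands, and it is why the size is given as a range that includes no inflation.

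A second reply is that the unit term may be left to a fuller analysis plan. This does not stand. The article names the primary model, its level and its covariate, discusses clustering and confines it to patient and staff outcomes, and sizes the trial as if wards were independent.

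A reader might also infer that the exploratory analysis of predictors ("This analysis will be performed using multiple linear regression") has the same fault. The article does not support that. The predictors are unspecified, and for one that varies between wards within a unit, ignoring clustering can make the standard error too large rather than too small.

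**Conclusion.** The stated primary analysis does not match the unit of randomisation and should be changed. The direction is clear for any positive residual ICC: the standard error is too small, the interval too narrow and the type I error above 5%. The size is uncertain: small at ICC 0.1, and roughly one and a half to somewhat over three times the nominal level at 0.3 to 0.5.

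Two stronger readings should be avoided. One is that the type I error certainly exceeds 5%; it does so only if the residual ICC is positive, which is likely but not quantified in the article. The other is that error rates of 12% to 20% are to be expected; these need an assumed unequal-size distribution together with ICCs of 0.3 to 0.7.

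Power is less of a worry, because 67 wards were followed up against 54 required. At ICC 0.3 a cluster-correct analysis would still have about 89% power with equal sizes (DE 1.29), or about 84% with an assumed coefficient of variation in unit size of 0.6. The harm is mainly to the p-value and the interval.

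**What to change.** Replace the primary model with a linear mixed model of 12-month QELS on arm, baseline QELS and the unit-size stratum used in randomisation. Include a random intercept for unit and small-sample degrees of freedom (Kenward–Roger or Satterthwaite) based on the 38 units. An ANCOVA on unit means with the same terms is an acceptable equivalent and a useful check. Report the estimated unit ICC and the distribution of wards per unit.

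The cost is in wording and analysis only. Residual degrees of freedom fall from 67 − 3 = 64 to about 38 − 3 = 35, or 34 with the stratum. The interval widens roughly by the √DE factors in the working: little if the ICC is near zero, about 11–26% at ICC 0.3. The Status of the trial section describes data cleaning as ongoing, so the article presents the analysis as still to come.

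The exploratory predictor regression should also allow for unit clustering. That is advisable but separate from the necessary change to the primary analysis.
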